**Appendix 13**

**Side Effects Questionnaire**

Rate these effects since your last visit.

0 = not at all, 1 = mild, 2 = moderate, 3 = severe

Dizziness*

Stomach upset*

Memory lapses

Sleepiness*

Irritability

General weakness*

Numbness in fingers or toes*

Muscle or joint pain*

Change in energy level

Tingling skin sensation*

Coughing*

Change in sex drive*

Difficulty swallowing

Abdominal pain*

Change in appetite

Sadness*

Headache*

Anxiety

Blurred vision*

Muscle spasm*

Any bleeding episode*

Bruises*

Jaundice*

Rash*

Inability to sleep

Muscle weakness or tenderness*

Is there any new medical issue since we last saw you?

*potential side effect of gemfibrozil

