Another potential threat to crossover designs is that participants will not remain blind to drug condition, which could bias their responses to the medication. Gemfibrozil is not psychoactive and has few side effects that distinguish it from placebo (see below). Even if participants are able to detect active drug versus placebo, results are not necessarily invalid. For example, Perkins et al. (2008, 2010a) reported that participants were not completely blinded to nicotine patch or varenicline. However, because correct identification of treatment condition did not differ according to quit interest of participants or reinforcement condition, Perkins et al. concluded that the observed therapeutic effect was not due to expectancy of benefit from the active medication.

Summary

The proposed study will be the first clinical evaluation of gemfibrozil as a novel medication for the treatment of tobacco dependence. We will use the screening methodology developed by Perkins et al. (2006, 2008, 2010a) to investigate the effect of gemfibrozil on smoking abstinence and on laboratory measures of nicotine reinforcement and cue-elicited craving. We will also examine the predictive relationship between these laboratory measures and smoking abstinence.

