*Genetic Blood Samples.* At the start of the study, a 20-ml blood sample will be obtained by venipuncture for genotyping. Examples of the genes of interest include, but are not limited to dopaminergic (DRD1-5), dopamine metabolic (COMT), nicotine metabolic (CYP2A6), nicotinic (CHRNA4-5, CHRNB2), and cannabinoid (CB1R) genes, all of which have been associated with tobacco addiction. Blood samples will be frozen and stored in a secure freezer used by the Translational Addiction Research Laboratory. Identifiers, such as name or date of birth, are not included with these samples.  Genetic data will be stored on a password protected computer in a locked room. The data files are also password protected.   Samples will be stored indefinitely as additional polymorphisms relevant to addiction may develop.  Exploratory genotyping may be undertaken to assess the role of other genes that future research suggests to be relevant to the purpose of this protocol. For example, a gene or a newly defined polymorphism may be suggested to affect processes related to nicotine reinforcement or cue-elicited tobacco craving. Any use of stored samples for future genetic testing will be brought to the REB for approval.

*Assessment visit.* Upon attending the clinical trial site at CAMH, the participant will first be requested to provide written informed consent. After obtaining consent, participants will be asked to provide general demographic information and detailed questions regarding their tobacco and other drug use (Appendix 5; Appendix 17). Participants will also be requested to undergo a psychiatric assessment (MINI; Beck Depression Inventory) and assessment of usage of psychiatric medications (concomitant medication; medication history). A complete medical history and physical exam will be conducted to assess general health and to assess screening criteria (e.g. adverse events and Appendix 13 at baseline). A blood and urine sample will also be taken to assess measures as outlined in Appendices 1 and 2.

*Medication collection visit.* During the first clinic visit of each 2-week phase, participants will collect their medication and complete a number of baseline questionnaires. During this visit, all participants will provide a breath carbon monoxide (CO) sample, report the number of cigarettes smoked over the past 24 hours, and complete the following baseline questionnaires:

1. Fagerström Test for Nicotine Dependence (FTND; Heatherton et al. 1991; Appendix 6)

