At each clinic visit during the study, participants will complete the Mood Form, TCQ-SF, MNWS, and provide a breath CO sample. Participants will be asked whether they think they are taking gemfibrozil or placebo. Additionally, participants will report whether they smoked over the past 24 hours. Breath CO < 5 ppm will be used to verify smoking abstinence (Marrone et al. 2011). Concomitant medication, adverse events and side effects (Appendix 13) will be assessed at each clinic visit.

Women must provide a negative urine pregnancy test at each clinic visit and must not be nursing because the effects of gemfibrozil on fetal and early development are not known.

During the study, participants will consume their normal caffeine intake and continue to take prescription medications, unless otherwise instructed by the Qualified Investigator. Participants will smoke normally and must not use any illicit drugs or alcohol 24 hours before experimental sessions. To ensure that participants are not under the influence of recent alcohol or drug consumption, their blood alcohol concentration (BAC) will be tested with a breathalyzer (Heishman et al., 1996, 1998). Participants must register a BAC of 0.000%. If participants fail the BAC, their session will be canceled, and they will not receive payment that day.

End of Participation and Follow Up

At the conclusion of the study, either the PI or his designee will meet with participants to answer any questions they might have about the study. This also serves as an opportunity to intervene with respect to the participant’s tobacco dependence. The investigator will counsel participants on the risks of continued smoking and the benefits of quitting and give them a referral list of smoking treatment programs.

We will call participants 1 week after the last medication phase to assess potential side effects (see Appendix 13) and their general health. The QI will review the follow-up assessment, and if there are no problems, the participant will be discharged from the study. Any medical concerns will be followed until a satisfactory resolution is reached.

Figure 1 provides a schematic of the study design

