Appendix 3 provides a schematic of the trial design

**Risks and Discomforts**

Minimal risks/discomforts

There is a minor risk of contact dermatitis as a result of the skin electrodes. Participants will likely experience increased tobacco craving after presentation of smoking cues. Because both Nic and Denic cigarettes are smoked during the forced-choice session, participants will not experience withdrawal. Smoking the equivalent of 4 cigarettes over 4 hours during the forced-choice session should pose little additional risk to current smokers. Because smoking is toxic to fetal development and because the effects of gemfibrozil on fetal development are not known, women must provide a negative urine pregnancy test before sessions and must not be nursing.

There is a possibility of discomfort at the site of needle entry for blood draws, and there is a risk of bruising. There is a remote risk of fainting or local infection. Trained phlebotomists and nurses using aseptic techniques will draw blood.

Participants might experience nicotine withdrawal during the quit-attempt weeks. This might include cigarette cravings, depressed mood, irritability, insomnia, anxiety, restlessness, difficulty concentrating, and increased appetite (DSM-IV symptoms of nicotine withdrawal, American Psychiatric Association 2000). These symptoms might increase the possibility of relapse to smoking.

Potential loss of confidentiality is a particular risk of studies involving genotyping. Under such circumstances, it could be a risk for genetic information about an individual to be made known. For example, genetic information could be informative to determine parentage or could be interpreted by an insurance company or employer to mean that the person was at increased risk for a problem. No genotype data will be released to subjects under any circumstance. In the study, there will be no identification of genetic diseases, and thus, no relevant information to report to subjects.

More than minimal risks/discomforts

The primary risks of this study involve gemfibrozil administration. In the Helsinki Heart Study, 2046 patients received gemfibrozil for up to 5 years. The adverse reactions that were statistically more frequent in the drug group compared with the placebo group were gastrointestinal reactions (34% vs. 24%), including dyspepsia and abdominal pain. Acute appendicitis (1.2% vs. 0.6%) and

Figure 1

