**Participant Safety Monitoring**

During screening, study applicants will undergo a complete battery of medical laboratory tests and physical exam to determine their eligibility and safety of their participation in this study (see Appendix 2). Study applicants will be excluded if they have any history of liver disease, abnormal renal function, diabetes, recent gallbladder disease or operation, or any other medical condition, or are on any medication that may contraindicate their participation in this study. During the treatment phase of the study, participants will be asked about side effects and adverse events at each clinic visit (Appendix 13). Additionally, CBC, complete metabolic panel, creatine kinase levels, PT/INR, and HbA1c will be assessed at screening and after at least 10 days on medication. The QI/PI ([name] [name]) will review side effect reports and medical tests. Participants will be discharged from the study if they have any signs or symptoms that may contraindicate continued drug administration.

If participants seek medical care during the study, they will be instructed to notify their physician or medical care provider of involvement in the study and the possibility that they may be taking gemfibrozil. We will follow up with participants 1 week after the last medication phase to assess potential side effects (see Appendix 13). The QI will review the follow-up assessment, and if there are no problems, the participant will be discharged from the study. Any medical concerns will be followed until a satisfactory resolution is reached.

Successful Quit Attempts: Ethical considerations

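### The Appendix 13 side-effect form, used at baseline and every clinic visit, prints a key to gemfibrozil's side effects: a minor, avoidable prompt against the blind

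*Protocol*

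**What the plan says.** Appendix 13 lists 26 symptoms to be scored 0 to 3 under the instruction "Rate these effects since your last visit". Many carry an asterisk, and the footnote reads "potential side effect of gemfibrozil".

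The form first appears at the assessment visit (Study Procedures: "e.g. adverse events and Appendix 13 at baseline"). It then recurs throughout: "Concomitant medication, adverse events and side effects (Appendix 13) will be assessed at each clinic visit". Participant Safety Monitoring repeats this for the treatment phase: "participants will be asked about side effects and adverse events at each clinic visit (Appendix 13"). It is also the instrument for the telephone follow-up one week after the last medication phase.

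The paragraph of Study Procedures that sets out the clinic-visit assessments has participants complete the Mood Form, the craving questionnaire and the withdrawal scale, and adds: "Participants will be asked whether they think they are taking gemfibrozil or placebo". No order is given for the guess, the scales and the side-effect form.

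Blinding and Unblinding calls the trial double-blind. The crossover considerations in the Introduction name loss of the blind as something that could bias responses, and offer the reassurance that "Gemfibrozil is not psychoactive and has few side effects that distinguish it from placebo".

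**The concern.** The form sorts symptoms, on its face, into those the drug may cause and the rest. It does so before the first capsule and again in both phases, at visits that also collect the treatment guess and self-reported outcomes.

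Three things are at stake. First, the treatment guess is the only check of the blind that the protocol describes, and a guess prompted by the trial's own form is a poorer check. Second, the primary cue-reactivity measures include self-reported craving and mood, which are open to expectancy. Third, the side-effect ratings themselves may drift towards the items marked as drug effects.

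The protocol treats loss of the blind as a threat and relies on the drug being hard to recognise, so a printed key to recognising it works against the protocol's own reasoning.

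**Working it through.** The protocol states no figure on this point, so there is none to reproduce. The check is a count, a comparison of passages and one illustration.

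**Count of items (Appendix 13).** There are 26 symptoms. Seven are unstarred: memory lapses, irritability, change in energy level, difficulty swallowing, change in appetite, anxiety and inability to sleep. That leaves 26 − 7 = 19 starred, and 19/26 = 73%.

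**Count of exposures.** Each phase has a medication collection visit, a laboratory visit and an abstinence visit. Read literally, the form is used at 1 assessment visit + 2 × 3 clinic visits = 7 visits, or more if the two laboratory sessions fall on separate days. The telephone call comes on top.

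**Who sees the legend.**
- The instruction, addressed to the person rating, suggests that the participant fills in the form. In that case the participant sees the stars.
- Participant Safety Monitoring and the medication instruction form (Appendix 4) say that participants are asked about side effects, and on the telephone they cannot see the page. In that case the staff member sees the stars.
- The protocol describes no copy without asterisks, does not place the guess before the form, and does not separate the staff who use the form from those who run the sessions. A blinded party therefore sees the legend in either mode.

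**Illustration of how informative one starred symptom could be.** Inputs from Risks and Discomforts: gastrointestinal reactions in 34% on gemfibrozil and 24% on placebo, in a study of up to 5 years' use. Write p1 = 0.34 and p0 = 0.24.

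- One phase, guessing gemfibrozil if the symptom occurs and placebo if not: 0.5 × p1 + 0.5 × (1 − p0) = 0.5 × 0.34 + 0.5 × 0.76 = 0.55.
- Both phases compared, guessing gemfibrozil for the phase with the symptom and tossing a coin on ties, with the phases taken as independent:
  - symptom only on gemfibrozil: 0.34 × 0.76 = 0.258
  - symptom only on placebo: 0.24 × 0.66 = 0.158
  - ties: 1 − 0.258 − 0.158 = 0.583 from unrounded values
  - accuracy: 0.258 + 0.5 × 0.583 = 0.55

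Both strategies reduce to 0.5 + (p1 − p0)/2 = 0.5 + 0.10/2 = 0.55, so for a single yes/no symptom the second phase does not raise average accuracy. The result is 5 percentage points above chance. It describes what anyone who knows that the drug can upset the stomach could achieve, with or without a starred form. The increment due to the stars is not in this figure, and no other figure in the protocol gives it.

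**The case against.** The best case for leaving the form alone has four parts, and most of it stands as a limit on the size of the problem.

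- **The participant may never see the stars.** The protocol speaks of participants being asked, and uses the same form by telephone. This stands: self-completion is suggested, not stated. It moves the exposure to blinded staff without removing it.
- **Staff knowledge does little harm.** No outcome is scored by a rater: puffs are chosen, scales are self-reported, and physiology and breath carbon monoxide are instrument readings. Staff also have the risk list in the protocol, and knowing a drug's profile is not knowing an allocation. This largely stands. What remains is that the staff who run the sessions handle the key at each visit.
- **Consent already discloses the risks.** The consent process covers gemfibrozil's side effects and a quiz tests understanding of procedures and risks. This stands, so the stars add prompting more than new information. A prompt symptom by symptom at every visit is still different from one disclosure at entry.
- **The key discriminates poorly.** With 73% of items starred and most of them non-specific, it tells the reader little. This also stands.

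A reader might go further and infer that the form separates drug effects from nicotine withdrawal, because irritability, anxiety, appetite change and sleeplessness are unstarred. The form does not support that: sadness is starred, although depressed mood is a withdrawal symptom in the protocol's own list. The laboratory measures are also taken before the quit week, while participants smoke normally.

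**Conclusion.** The point holds as a minor, avoidable weakness. A form used at baseline and at each clinic visit of a double-blind crossover prints a key to the active drug's side effects, and a blinded party sees it whichever way the form is administered. It could raise correct guessing and tilt side-effect ratings towards starred items. The effect of the legend itself is likely modest and cannot be quantified from the protocol.

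Several stronger readings do not follow:

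- That participants are given the key, or that the blind is broken: the mode of administration is not stated, and nothing shows actual unblinding.
- That 55% correct guessing measures the harm: it rests on rates from up to 5 years' use, against 2-week phases here, and on the drug's detectability rather than the legend. The protocol gives no rates for most other starred symptoms, so it does not show that they add to this figure.
- That all primary outcomes are exposed: autonomic responses are not self-reported, and no route from a treatment guess to choosing nicotine over denicotinized puffs is shown.
- That the Introduction's argument on blinding must be deleted: it says only that detection need not invalidate results. Whether its supporting studies carry over to this design is a separate matter.

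The conclusion assumes that the visit copy is Appendix 13 as printed, since the protocol describes no other.

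**What to change.** Remove the asterisks and the footnote from the copy of Appendix 13 used at visits, in the telephone call and by any blinded staff. Keep the list of suspected gemfibrozil effects in a separate document for safety review, where the same 26 ratings can be read against it.

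State in Study Procedures that, at each visit, the treatment guess and the self-report scales are collected before the side-effect form. The order alone would not be enough, because participants meet the form at baseline and carry it into later visits. Removing the legend does most of the work.

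It would also help to say whether the participant or staff complete the form, so that the mode is the same in both phases.

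The cost is a form revision and a sentence or two on order and mode of completion. No item, visit, procedure, analysis or sample size changes, and no safety information is lost.

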**Appendix 15: Daily Call Materials**

**Instructions for Daily Calls**

**Each evening when you take your medication please call [contact] [name] after you take your study medication.** This call should be placed immediately following taking your medication. Listen carefully to the message on the phone and follow the instructions. You will answer the questions below.

You will **read** off **each question letter** on the left and **then answer** with **your response**.

| **#** | **Question** | **Possible Answers** |
| --- | --- | --- |
| **A** | Did you take your medication this morning? | Yes No |
| **B** | Did you take your medication this evening? | Yes No |
| **C** | How many cigarettes have you smoked in the past 24 hours? |  |

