**Précis**

Summary

*Objectives*

Animal studies have shown that drugs acting as agonists at alpha-type peroxisome proliferator-activated receptors (PPARα) suppress nicotine self-administration, attenuate relapse to nicotine-seeking behavior in the reinstatement model, and block nicotine-induced neuronal firing and dopamine release in reward pathways of the brain. These results have been demonstrated with synthetic PPARα agonists and with fibrate drugs (clofibrate, fenofibrate), which are used clinically to treat elevated cholesterol and triglycerides levels. Thus, PPARα is a potential target for the treatment of tobacco addiction. This is the first human study to investigate whether a fibrate drug (gemfibrozil, Lopid®) can reduce nicotine reward and aid smokers in becoming tobacco abstinent.

The objectives of this study are:

1. to investigate the effect of gemfibrozil on laboratory measures of nicotine reinforcement and cue-elicited craving
2. to screen for the ability of gemfibrozil to aid smoking abstinence during a brief quit attempt
3. to examine the validity of using laboratory measures of tobacco dependence to predict smoking abstinence and possible gemfibrozil-related increases in smoking abstinence

*Study population*

This outpatient study will be conducted at the Center for Addiction and Mental Health (CAMH) in Toronto, Canada. This site will enroll 40 adult smokers who intend to quit smoking in the next 3 months.

*Design*

The study is a double-blind, placebo-controlled, crossover design comparing the effects of gemfibrozil and placebo. The study will comprise two 2-week medication phases with a washout period of at least one week. At the end of the first medication week laboratory measures will be taken and during the second medication week participants will make a quit attempt and abstinence will be assessed.

*Outcome Measures*

Primary outcome measures include laboratory assessments of nicotine reinforcement and smoking cue reactivity. The measure of nicotine reinforcement is the percentage of nicotine cigarette puffs chosen during a forced-choice task. Measures of cue reactivity include tobacco craving, mood, and autonomic responsivity.

The secondary outcome measure is days of smoking abstinence during the quit-attempt weeks. Abstinence is assessed by self-reports of no smoking and by breath carbon monoxide < 5 ppm on clinic visits. Other assessments of abstinence include self-reported tobacco craving and withdrawal.

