*Gemfibrozil/placebo dosing.* Lopid® (gemfibrozil, USP) tablets, each containing 600 mg gemfibrozil, will be supplied by Pfizer, Inc. CAMH Research Pharmacy will formulate the tablets into capsules and dispense to participants in blister packs. Gemfibrozil will be dosed as clinically indicated, 600 mg twice daily and orally, taken 30 minutes before the morning and evening meals. The participants will take 1 capsule of 600 mg at a time. Placebo capsules containing only lactose will follow the same regimen. A medication instruction form will be given to participants (Appendix 4)

*Medication compliance*. Medication compliance will be monitored by requiring participants to call into a dedicated phone line once a day when they have taken their second capsule; at this time they will also indicate the number of cigarettes they have smoked that day. Medication compliance will also be verified by requiring participants to return the blister packs, allowing staff to conduct a pill count verifying the number of doses taken. Finally, as described below, a blood sample will be taken in order to verify the levels of gemfibrozil in the body.

*Blood samples*. During the initial visits where eligibility for inclusion in the study will be assessed, a blood sample will be drawn to assess measures including serum glucose, serum creatinine, creatine kinase, complete blood counts, liver function tests, PT/INR and HbA1c as outlined in Appendix 2.

Two samples of blood will be drawn after at least 10 days on medication and during each phase. One blood sample will be processed for subsequent quantitative analysis of gemfibrozil concentration. Blood samples will be stored in a secure -80 freezer. A few placebo samples will be sent to the laboratory for testing to insure the specificity of the assay. Plasma samples will be destroyed after analyses are completed. Additionally, the other blood sample will be drawn for medical safety monitoring (CBC, BUN/Cr, CK, PT/INR, HbA1c, and LFTs) to monitor any hematologic changes or change in renal/liver function.

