*b) Forced-choice.* The forced-choice session occurs later that same afternoon. After a brief lunch period, participants will smoke 4 puffs from their preferred-brand cigarette and then relax (read or listen to music) for 30 minutes, during which they are not allowed to smoke. They then complete baseline self-report measures (TCQ-SF, Mood Form, VAS) and give a breath CO sample. The forced-choice session consists of exposure trials and choice trials. During exposure trials, participants sample the Nic and Denic cigarettes. Exposure order will be counterbalanced across subjects, and each cigarette will be sampled twice for a total of 4 trials, using either an ABAB or BABA order. At 30-minute intervals, participants smoke 4 puffs from the designated cigarette. After each exposure trial, participants rate the puffs using the modified Cigarette Evaluation Questionnaire (mCEQ; Cappelleri et al. 2007; Appendix 12). The choice trials begin 30 minutes after the last exposure trial. There are 4 forced-choice trials occurring at 30-minute intervals; participants choose any combination of 4 puffs from the two cigarettes at each trial. During intervals between exposure and choice trials, participants can read or listen to music. The smoking rate during the entire session (8 puffs every 60 minutes) is less than that of the typical ad libitum smoking pattern of a daily smoker of one cigarette (10 puffs) every 30-40 minutes (Hatsukami et al. 1988). At the end of the session, participants give a breath CO sample and complete the TCQ-SF, Mood Form, and VAS.

*Abstinence visit*. Participants will then visit the clinic again one week after the laboratory session to assess abstinence following the 1 week quit attempt while on medication. In this visit, they will be administered a number of questionnaires, their CO measures taken and questions about adverse events will be asked.

During the medication phase of the study, participants will call the clinic each day to report that they have taken their medication and the number of cigarettes that they have smoked that day.

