**Outcome measures**

Primary outcome measures include laboratory assessments of nicotine reinforcement and smoking cue reactivity. The measure of nicotine reinforcement is the percentage of nicotine cigarette puffs chosen during the forced-choice task. Measures of cue reactivity include tobacco craving, mood, and autonomic responsivity.

The secondary outcome measure is days of smoking abstinence during the quit-attempt weeks. Abstinence is assessed by self-reports of no smoking and by breath carbon monoxide < 5 ppm. Other assessments of abstinence include self-reported tobacco craving and withdrawal.

Sociodemographic and baseline measures (e.g., smoking history, level of nicotine dependence, number of cigarettes smoked per day, tobacco craving, mood, smoking motivations) will be used to characterize the sample and explore as mediators of primary and secondary outcomes.

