**Call the lab**

Each time you take your evening pill, call [contact] [name] and leave a message telling us the time you took the pill. At the evening call, you will answer a few questions about any smoking. You will earn $2 per day for taking the pills, calling us in the evening, and answering the questions.

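### The daily call asks for a number of cigarettes, not whether the participant smoked at all, so puff-only days in the quit week may be counted as abstinent

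*Protocol*

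**What the plan says.** **The outcome.** Under Outcome measures, "The secondary outcome measure is days of smoking abstinence during the quit-attempt weeks". The same section defines the state being counted: "Abstinence is assessed by self-reports of no smoking and by breath carbon monoxide < 5 ppm". The Précis adds that CO is taken at clinic visits.

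**The daily record.** Study Procedures (Medication compliance) has participants phone in once a day after the second capsule, and "at this time they will also indicate the number of cigarettes they have smoked that day". The paragraph after Abstinence visit repeats this as "the number of cigarettes that they have smoked that day". Appendix 15 gives the call card: two yes/no items on medication and one smoking item, "How many cigarettes have you smoked in the past 24 hours", with a blank answer field. Appendix 4 (Call the lab) describes the same call differently: "At the evening call, you will answer a few questions about any smoking".

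**The visit record.** At each clinic visit "participants will report whether they smoked over the past 24 hours", and a CO sample is taken. Appendix 3 shows one clinic visit for each quit week, at its end. The timeline follow back is cited at the assessment visit and listed for the medication collection visits. It is not named for the abstinence visit, and its form is not shown.

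**The concern.** A count of cigarettes and a report of not smoking are different measurements. They agree on a day with no smoking and on a day with several whole cigarettes. They can disagree on a lapse day, when someone takes a few puffs of another person's cigarette or smokes half of one. Under the stated definition that is a smoking day. Asked how many cigarettes, the participant may answer 0, a fraction, 1, or describe the puffs; the card gives no guidance.

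Days abstinent carries Aim 2 and hypothesis 3. It is also the quantity to be predicted in Aim 3 and hypotheses 4 and 5. The hypothesised action of gemfibrozil is reduced nicotine reinforcement, which could plausibly change how far a lapse goes as well as whether it occurs. Error at the boundary between no smoking and a little smoking therefore need not be the same in the two phases.

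**Working it through.** **1. What covers each quit-week day.** The plan gives no figure to reproduce here, so the first step is to set the sources side by side.

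| Source | Asks about any smoking? | Quit-week days covered |
|---|---|---|
| Evening call (Appendix 15, item C) | No, number of cigarettes only | All seven |
| Clinic-visit question | Yes | Past 24 hours: about the last day |
| Breath CO | Biochemical check | One reading, at the end of the week |
| Timeline follow back | Content not shown | Not named for the abstinence visit |

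The timeline follow back at the second medication collection visit could reach back to the first quit week. Appendix 3 shows no medication collection visit after the second quit week. For about six of the seven days, the call count is the only daily smoking record described.

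**2. Size of the possible error.** The documents give no share of puff-only days, so this step is an illustration.

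Inputs: mean days abstinent from the two cited screening studies (Brief Assessment of Smoking Abstinence), 1.1 on placebo and 2.0 on nicotine patch, and 1.5 on placebo and 2.6 on varenicline, taken as true values; a seven-day quit week; and q, the share of non-abstinent days that are puff-only and reported as 0, *assumed* to be 5%, 10% or 20%.

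Formula: counted days = A + q(7 − A), where A is true days abstinent.

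Placebo level:
- A = 1.1: 1.1 + 0.05 × 5.9 = 1.40; 1.69 at 10%; 2.28 at 20%.
- A = 1.5: 1.5 + 0.05 × 5.5 = 1.775; 2.05 at 10%; 2.60 at 20%.

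**3. Same q in both phases.** The difference becomes (A_drug − A_placebo)(1 − q).
- Patch figures: 0.90 becomes 0.855, 0.81 and 0.72.
- Varenicline figures: 1.10 becomes 1.045, 0.99 and 0.88.

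The effect is diluted by exactly q.

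**4. Different q in the two phases.** The bias is q_drug(7 − A_drug) − q_placebo(7 − A_placebo).

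No true effect, q differing by 10 points: 0.10 × 5.9 = 0.59 days, or 0.10 × 5.5 = 0.55 days. The sign follows whichever phase has the larger share. Against the cited effects, 0.59/0.9 = 66% and 0.55/1.1 = 50%.

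True effect as in the cited studies, with shares of 10% and 20%:

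| Figures | True difference | Placebo 10%, drug 20% | Placebo 20%, drug 10% |
|---|---|---|---|
| Patch | 0.90 | 3.00 − 1.69 = 1.31 (+0.41) | 2.50 − 2.28 = 0.22 (−0.68) |
| Varenicline | 1.10 | 3.48 − 2.05 = 1.43 (+0.33) | 3.04 − 2.60 = 0.44 (−0.66) |

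The two directions are not symmetric here because dilution acts in both.

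**The case against.** The protocol nowhere says that a puff scores 0, or that a reported 0 alone makes a day abstinent. Its definition is no smoking plus CO, and under that a puff day is not abstinent. The answer field is open, so a participant may mention puffs or a half. Appendix 4 tells participants that the call is about any smoking, which works against a whole-cigarettes-only reading. Appendix 15 also refers callers to a recorded message that is not reproduced. The call is introduced as a compliance measure, while the abstinence visit is where abstinence is said to be assessed. Turning call data into abstinent days may be set out in an analysis plan that is not shown. Finally, if misreporting is equal in the two phases, the bias is towards no difference.

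Much of this stands, and it limits what can be claimed. A reader might infer that the plan scores puff days as abstinent; the documents do not support that, only that such days may be recorded that way. A reader might also infer that the error flatters gemfibrozil. Nothing in the documents fixes its direction, and the reverse case cuts the patch-study difference from 0.90 to 0.22 days.

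The gap in the instrument remains. An analysis plan can decide how to score a reported 0, but it cannot recover smoking that nobody asked about. The wording in Appendix 4 adds a discrepancy, because it announces several questions where Appendix 15 has one.

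**Conclusion.** The point holds as a mismatch between instrument and definition. Abstinence means no smoking, while the only daily record described asks for a number of cigarettes. On about six of the seven quit-week days, no other any-smoking question or CO reading is described, so puff-only or part-cigarette days may be counted as abstinent.

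The size is unknown. Under the assumed shares of 5–20%, equal error dilutes the drug–placebo difference by 5–20%. A 10-point gap between phases with no true effect gives 0.55–0.59 days in either direction, which is 50–66% of the effects in the cited studies. These figures rest on the assumed shares, on taking the cited means as true, and on a reported 0 being scored as abstinent without further check.

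The affected outcome is secondary, although Aim 3 also uses it. The primary laboratory outcomes are untouched. This is an inexpensive improvement worth making, not a flaw that invalidates the design.

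**What to change.** Add a yes/no item to the call card and the recorded message, such as *In the past 24 hours, have you smoked at all, even a puff?* Keep the count after it and say how part-cigarettes are to be reported. A fixed 24-hour window is safer than asking about the time since the last call, because a missed call would then merge two days into one answer.

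Score a quit-week day as abstinent only if the answer is No, with CO below 5 ppm also required where it was measured. Use the same wording at the abstinence visit. Bring Medication compliance, the daily-call paragraph after Abstinence visit, Appendix 4 and Appendix 15 into line on what the call asks and over what period.

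Cost: one extra line on the call and a minor ethics board amendment. Abstinence counts will be slightly lower, and the measure will not be identical for participants already through the study. Record which version each participant answered, and where possible keep one version across both phases for the same person, so that the change of wording does not enter the within-person comparison.
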